#### Secondary Outcome Measures

##### ACT Survey to Assess Secondary Outcomes

Recognizing that ACT scores may improve but remain ≤19 for some participants with poorly controlled asthma, we will also assess for change in the ACT score that is considered clinically important (as indicated by a ≥3-point increase) [23]. The ACT score will be assessed via a mobile survey to measure for sustained improvement throughout the study. We hypothesize that PCP data sharing will facilitate asthma control by alerting the PCP when asthma worsens or fails to improve. The impact of PCP data sharing on the ACT score will be measured to assess whether data sharing has added any benefit to the PEAKmAAP group.

##### Composite Asthma Severity Index

The Composite Asthma Severity Index (CASI), a comprehensive scale reflecting impairment, future risk, and the level of treatment needed to maintain control, has been developed to align with the new concept recommended in *Expert Panel Report 3: Guidelines for the Diagnosis and Management of Asthma* (EPR-3) [2]. The integral CASI instrument has 5 domains: day symptoms and albuterol use, night symptoms and albuterol use, controller medication, lung function measures, and exacerbations. CASI is considered a better discriminator of treatment response than a symptom-based outcome. Thus, as an alternative to the ACT score, CASI will be also used to quantify asthma severity and prospectively gauge asthma control in the proposed study.

##### Medication Use

Self-reported rescue medication use will be assessed via a mobile survey. Participants will be asked, “How many days/nights in the past 2 weeks did you use ___ (rescue medication name) because you were wheezing, coughing, or having trouble breathing?” These data will be collected for all participants and will be used to generate a PCP report for PEAKmAAP-DS participants.

##### Health Care Use

Self-reported health care use will be assessed monthly via a mobile survey. Participants will record exacerbations resulting in hospitalization, ED or sick visits, or prednisone use. These data will be collected for all participants and will be used to generate a PCP report for PEAKmAAP-DS participants.

##### Lung Function and Airway Inflammation

Spirometry is the test most used for the assessment of the risk for adverse events (AEs) and impairment in asthma [2]. The forced expiratory volume in the first second (FEV1) expressed as a percentage predictive of the reference population value or as a proportion of the forced vital capacity (FEV1/FVC) will be assessed. Fractional exhaled nitric oxide (FeNO) is a quantitative, noninvasive measure of airway inflammation that predicts responsiveness and adherence to inhaled corticosteroids (ICS) [41-43]. We will measure lung function and FeNO at baseline, 3 months, and 12 months for all participants.

##### Child Self-Efficacy Survey.

The Child Self-Efficacy Survey is a 9-item validated questionnaire and is designed to measure a child’s self-efficacy with regard to attack prevention and attack management [44]. The participants will be required to select 1 of 4 responses ranging from “none of the time” (0 points) to “all of the time” (3 points). The survey will be administered at baseline, 3 months, and at the end of the intervention for all participants. The reliability of the survey (Cronbach α) is .75.

##### Asthma Control Classification

Asthma guidelines categorize asthma control for individuals ≥12 years old into 3 categories: well-controlled (WC), not well-controlled (NWC), or very poorly controlled (VPC) [2]. Asthma control is defined by the degree to which asthma manifestations are minimized by therapeutic intervention [2]. Components of asthma control include measures of daytime symptoms, nighttime awakenings, activity limits, rescue medication use, and exacerbations requiring oral systemic corticosteroids. An assessment of asthma control will be performed during the eligibility screening; at the in-person, structured interviews at baseline, 3 months, and 12 months; and via a mobile survey at 6 and 9 months for all participants.

##### Medication Adherence

Using prescription refill data, we will compare adherence prior to enrollment with adherence during the study period. We have successfully attained prescription refill data in our previous studies. Participants will provide written release of information during the consent interview. In addition, these data are frequently requested by providers as a component of usual patient care in Primary Care Medical Home (PCMH) clinics. Adherence will be defined as receiving ≥3 controller medication refills/6 months or achieving an asthma medication ratio (AMR) of ≥0.5 based on national asthma guidelines [2]. The AMR will be calculated as the ratio of the number of controller medications dispensed during a 6-month period divided by the sum of controller plus rescue medications dispensed during the 6-month period. An AMR of ≥0.5 has been associated with improved asthma outcomes [45]. The proportion of days covered (PDC) will also be assessed and compared between groups from prescription refill data. This measurement is defined by the number of days in the period covered divided by the number of days in the total period and is suitable for medication regimens that require multiple medications, such as asthma. Prescription refill data will be captured from the participants’ medical record dispense report via Magellan (a Medicaid vendor) or via a private pharmacy. We may also contact the participants’ local pharmacy used to obtain the pharmacy profile.

##### Medication Changes

To monitor for step-up or step-down in prescribed controller medications, medication changes will be assessed at each in-person visit at 3 and 12 months, by medical record review, and by prescription refill data. Participants will be advised to notify study staff of any medication changes.

### Data Collection and Management

We will use the Research Electronic Data Capture (REDCap) program. Data from the study will be checked for errors, inconsistencies, and missing data. We will examine the data graphically using scatterplots for continuous outcomes and frequency tables for categorical data. Unresolved data anomalies will be sent to the primary investigator for verification. Obvious outliers due to data entry errors will be corrected before data analysis begins. Different data sources will be linked using a unique identifier assigned to each participant.

### Adverse Event Reporting

All subjects will be monitored for AEs related to study procedures. Study investigators acknowledge that participants may experience asthma symptoms or exacerbations throughout the course of the study; however, exacerbations are expected due to the nature of the disease and not due to study-related procedures. Due to an intrinsic exacerbation risk to all patients with asthma, we will advise participants to continue to use medications as prescribed by their PCP and to keep their regularly scheduled visits. The research team will also conduct research review meetings on a weekly basis to monitor the progress of the study, ensure participant safety, discuss any unanticipated problems, ensure treatment integrity, and ensure that recruitment and study goals are being met, as well as solve any issues pertaining to enrollment, recruitment, or completion of study procedures. A Safety Monitoring Committee (SMC) will independently monitor participant safety. The SMC, consisting of a biostatistician and an independent clinical research investigator, will meet no less than once a year and as needed to discuss any potential safety concerns related to the research. All participants will be screened for AEs and serious adverse events (SAEs) at each study visit. They will be asked about asthma- and non–asthma-related health issues. All clinically significant AEs will be brought to the attention of the PI, who will categorize the AEs as “expected” or “unexpected” and as “likely” or “unlikely” to be related to the study. The PI will monitor all related AEs and SAEs. All AEs and SAEs will be entered into the study database and, as required, reported to the University of Arkansas for Medical Sciences Institutional Review Board, the SMC, or the National Institutes of Health (NIH). Because the interventions are adjuncts to ongoing clinical care and all participants are encouraged to continue to engage with their PCP, no formal ancillary or posttrial care is planned. Similarly, given the low risk of the interventions and continued PCP care, there are no criteria for discontinuing or modifying allocated interventions beyond a participant’s personal decision to discontinue participation in the study.

### Statistical Analysis

Primary models using the intent-to-treat (ITT) principle will be performed for all primary and secondary outcomes. All subjects will be considered part of their assigned treatment groups irrespective of their adherence to treatment, and all randomized subjects will be included in the analysis. Secondary models using a per protocol (PP) population including only participants who adhered to the protocol will be conducted. As appropriate, models will be adjusted for the baseline value of the outcome, with other baseline confounding or covariate variables included. Secondary subgroup analyses will stratify by baseline asthma control classification (poorly controlled vs not well controlled) defined by ACT scores. Holm-Bonferroni correction will be used to control the overall familywise error rate under 5% for analyses with multiple comparisons. Missing data in primary and secondary models will be handled by multiple imputation if “missing at random” is a reasonable assumption. Results will also be reported discarding missing values as a sensitivity analysis.

Using these models, the primary outcome of the proportion of participants with ACT scores of >19 at 3 months will be analyzed using linear models with a logit link function and contrasts to compare the 2 PEAKmAAP groups combined with the eUC group. Secondary analyses of the proportion of ACT scores of >19 at additional timepoints (6, 9, 12 months) will be assessed with contrasts for the group effect (to measure the average effect across the different timepoints) and the group-by-time interaction effect (to measure the change in effect over time) between groups (PEAKmAAP-DS vs PEAKmAAP; PEAKmAAP groups combined vs eUC). Since the ACT score will be measured at 3, 6, 9, and 12 months (all participants will have baseline scores of ≤19), these correlated repeated measures data will be analyzed with a binomial distribution and a logit link function for modeling with an appropriate correlation structure (eg, compound symmetry or first-order autoregressive). Additionally, minimally important improvements in ACT scores (3-point increase) and CASI (1-point decrease) will be similarly modeled as binary outcomes across timepoints, contrasting eUC versus the 2 PEAKmAAP groups combined or PEAKmAAP versus PEAKmAAP-DS. Other secondary outcomes (health care use, rescue medication use, lung function) will be analyzed using similar models for nonnormal data using appropriate distributions and link functions.

Medication adherence rates at 12 months will be compared using a logistic regression model after adjusting for baseline values as a covariate, contrasting eUC against the 2 PEAKmAAP groups. Mean asthma self-efficacy scores at 3 and 12 months, including the subscales for prevention and management, will be compared among the 3 groups using the analysis of covariance model after adjusting for baseline values as a covariate in the model. The proportion of adolescents who receive step-up therapy will be compared between the 2 PEAKmAAP groups, and the 2 PEAKmAAP groups together will be compared with the eUC across different timepoints using a similar logistic model.

No interim analyses are planned, and thus, there is no planned stopping rule for the study.

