## Methods

### Study Design

The study is a 3-arm RCT with adolescents with uncontrolled asthma (Figure 1). The study will be conducted at the Arkansas Children’s Hospital (ACH), with children receiving asthma care at ACH primary and specialty care clinics. A sample of 370 adolescents (age 12-20 years) and their caregivers will be enrolled. Participants will be randomized 1:1:1 to 1 of 3 groups: (1) a group using PEAKmAAP alone, (2) a group using PEAKmAAP with data sharing (PEAKmAAP-DS), and (3) an eUC group using an app with nonasthma daily reminders. Randomization will be stratified according to 2 strata based on asthma severity status (mild persistent and moderate-to-severe persistent) in order to minimize differences in baseline severity that may potentially bias treatment effects. A 1:1:1 permuted block randomization scheme with varying block sizes will be independently generated by our biostatisticians using nQuery Advisor 7.0 within each stratum to conceal allocation. The randomization list will be kept independent of the research staff to ensure allocation concealment.

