#### Baseline Visit

Research personnel obtained informed consent and assent from caregivers and adolescent participants, respectively, prior to any study procedures. At the initial visit, baseline data collection included lung function testing, frequency of asthma symptoms, activity limitations, health care use, asthma self-efficacy, and assessment of the dose and frequency of asthma rescue and controller medication. After these baseline data were obtained, participants were randomized to 1 of the 3 arms of the study. After randomization, PEAKmAAP and PEAKmAAP-DS participants received detailed instructions for use of the PEAKmAAP app, including an instructional video to explain all the features of the app, while the eUC participants received detailed instructions for the use of Nutrimap (Table 4).

**Table 4 table4:** Summary of study visit, outcome measures, and survey documents.

Measure	Screening prerandomization	Baseline prerandomization	3 months	6 months	9 months	12 months
Eligibility	X^a^	—^b^	—	—	—	—
ACT^c^ survey	X	Screening ACT score	X^d^	X	X	X^e^
Asthma severity classification	—	X	—	—	—	—
CASI^f^ score	—	X	X	—	—	X^e^
Lung function test with fraction of FeNO^g^	—	X	X^e^	—	—	X^e^
Child Self-Efficacy Survey	—	X	X^e^	—	—	X^e^
Asthma control classification (derived from the ACT survey)	—	X	X^e^	X	X	X^e^
Medication adherence (prescription profile for prior 12 months)	—	X^h^	—	—	—	X^h^
System Usability Scale (SUS)	—	—	—	—	—	X
Medication use (monthly self-report)	—	X	Monthly	Monthly	Monthly	Monthly
Health care use (monthly self-report)	—	X	Monthly	Monthly	Monthly	Monthly

^a^X: applicable.

^b^Not applicable.

^c^ACT: Asthma Control Test.

^d^Primary outcome.

^e^Outcome obtained by blinded research personnel at an in-person visit (all others via a mobile survey).

^f^CASI: Composite Asthma Severity Index.

^g^FeNO: fractional exhaled nitric oxide.

^h^Profile requested directly from insurer, pharmacy data, or medical record.

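### The subgroup analysis is described only as stratified by baseline control class and names no treatment-by-class contrast, so as written it cannot test whether the effect differs between classes

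*Protocol article*

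**What the plan says.** Under Statistical Analysis, the protocol article states: "Secondary subgroup analyses will stratify by baseline asthma control classification (poorly controlled vs not well controlled) defined by ACT scores". No comparison of treatment effects between the two classes is named. The longitudinal models do include an interaction, but a different one: "the group-by-time interaction effect (to measure the change in effect over time) between groups". On multiplicity, the same section says: "Holm-Bonferroni correction will be used to control the overall familywise error rate under 5% for analyses with multiple comparisons". Randomization is stratified by another variable: "Randomization will be stratified according to 2 strata based on asthma severity status".

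The class itself is described in three places:

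- Statistical Analysis (quoted above): two levels, taken from ACT scores.
- Table 4: "Asthma control classification (derived from the ACT survey".
- Asthma Control Classification: guideline categories, sorted "into 3 categories: well-controlled (WC), not well-controlled (NWC), or very poorly controlled (VPC", followed by "Components of asthma control include measures of daytime symptoms, nighttime awakenings, activity limits, rescue medication use, and exacerbations requiring oral systemic corticosteroids".

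**The concern.** An analysis run separately by class gives two treatment effects, each with its own interval and p-value. Whether the app helps one class more than the other is a question about the difference between those effects, and neither stratum result answers it. The trial is sized for at least 80% power on the whole sample, so each class alone has much less. Chance alone can then make one class significant and the other not, even if the effect is identical. A reader could easily take that pattern as evidence about which adolescents benefit.

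A smaller problem is that the article does not describe the class consistently. Two places take it from the ACT. The outcome section describes guideline categories with components beyond an ACT score, and its labels do not match those of the subgroup analysis.

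**Working it through.** **Inputs from the article (Study Design; Sample Size and Power Calculation).** Allocation is 1:1:1, so the combined app groups against eUC is 2:1. Before attrition there are 107 per group, for at least 80% power at two-sided 5%. The effect is 15% higher control at 3 months, read here as 15 percentage points.

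**Assumed, because the article does not state them.** The eUC control rate (20 to 40%), the split of participants between classes (50/50 to 80/20), and the same true effect in both classes. The evaluable 107 per group stands for the information available, although the plan includes all randomized participants with multiple imputation.

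**The plan's own figure.** The article gives no eUC rate or correlation, so 107 cannot be strictly reproduced. It is consistent with 20% vs 35% at 2:1: the required eUC size is 106, and power at 107 vs 214 is 80.6%. At eUC 40%, power would be about 72%. The article gives no power figure for the subgroup analysis.

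**Step 1: power per class, normal approximation.** At 80% overall power the overall z statistic has mean D = 1.96 + 0.84 = 2.80. A class holding share f of the sample has mean z = 2.80√f, and its power is P = Φ(2.80√f − 1.96), the opposite tail being negligible. The chance that exactly one class is significant is P1(1 − P2) + P2(1 − P1).

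| Split | Power in the two classes | Exactly one significant, unadjusted | Same, Holm across the two |
|---|---|---|---|
| 50/50 | 51%, 51% | 50% | 39% |
| 70/30 | 65%, 34% | 55% | 44% |
| 80/20 | 71%, 24% | 61% | 51% |

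With Holm, exactly one class is declared significant if its p-value is at or below 0.025 and the other's is above 0.05. At 50/50, power at the 0.025 level is Φ(1.98 − 2.24) = 0.397, so the probability is 2 × 0.397 × (1 − 0.508) = 0.39.

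**Step 2: check on the binary scale.** Take 53.5 eUC vs 107 app participants per class (50/50), 20% vs 35%. The pooled rate is (0.20 + 2 × 0.35)/3 = 0.30. The null standard error is √[0.30 × 0.70 × (1/53.5 + 1/107)] = 0.0767. The alternative standard error is √(0.16/53.5 + 0.2275/107) = 0.0715. Power is Φ[(0.15 − 1.96 × 0.0767)/0.0715] = 0.498, and discordance is 2 × 0.498 × 0.502 = 0.50.

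The same calculation at other settings, unadjusted:

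| eUC rate | 50/50 | 70/30 |
|---|---|---|
| 20% | 50.0% | 55.4% |
| 30% | 49.4% | 53.6% |
| 40% | 49.1% | 52.8% |

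The 49% lower end comes from this table and the 61% upper end from the 80/20 row in step 1. The Holm figures assume 80% overall power and are slightly lower where overall power is lower.

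**Step 3: no effect in either class.** Unadjusted: 2 × 0.05 × 0.95 = 9.5%. With Holm: 2 × 0.025 × 0.95 = 4.75%.

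**Step 4: the interaction test.** With equal effects, one million simulated trials per split gave a false-positive rate of 5.0% at every split. If the two class effects differ by as much as the overall effect, the interaction z has mean 2.80√[f(1 − f)]. At 50/50, power is Φ(1.40 − 1.96) = 29%. At 70/30, it is Φ(1.28 − 1.96) = 25%.

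**Step 5: the class descriptions side by side.** Table 4 and the Statistical Analysis section agree that the class comes from the ACT. The Asthma Control Classification section lists items such as steroid-treated exacerbations, which the monthly survey records separately from the ACT. Its lowest category is labelled very poorly controlled, while the subgroup sentence says poorly controlled. Three categories against two levels need not conflict, since "all participants will have baseline scores of ≤19" and an ACT-derived baseline class would leave the well-controlled category empty.

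**The case against.** The strongest reply is that the text neither rules out an interaction test nor says that classes will be compared by their separate p-values. This is a condensed article, and a statistical analysis plan may exist that supplies the test. That stands as a limit. A reader might infer that the investigators intend to claim benefit in one class from stratum-specific significance; the article does not say so. What remains is that it states a method, stratification, that does not answer the subgroup question, and names an interaction only with time.

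A reader might also infer that subgroup differences in this trial will usually be spurious. The article does not support that either. The 39 to 61% range requires a real effect of the design size, equal in both classes, and someone comparing significance across them. The Holm-Bonferroni rule, if applied across the two classes, lowers the discordance but does not remove it.

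Two further inferences fail. The loose description of the class leaves room for analyst choice, but it does not by itself create false subgroup differences, and the subgroup sentence does say that ACT scores define the class. Nor is the fixed ACT cut at 19 a defect here. Participants with lower baseline scores must gain more to cross it, but that does not bias the randomized comparison within a class, and the plan adds an outcome based on a 3-point ACT gain.

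**Conclusion.** The point holds in limited form. As written, the subgroup analysis cannot test whether the effect differs between control classes. If stratum results were nevertheless compared by significance, a homogeneous effect at the design value would look discordant in about 49 to 61% of trials unadjusted and about 39 to 51% with Holm, against about 5 to 10% with no effect. These figures rest on assumed eUC rates and class splits, on reading 15% as absolute points, and on independent classes. The inconsistent description of the class is a secondary matter of wording. The primary analysis is not affected.

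**What to change.** Replace the stratified analysis with one model in the full intention-to-treat sample that includes a treatment-by-baseline-class interaction, or an interaction with continuous screening ACT. Report the interaction estimate with its confidence interval, show class-specific estimates with intervals beside it, and state that no claim of differential benefit will be drawn from within-class p-values. Label the result exploratory.

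Reconcile the Asthma Control Classification section with Table 4 and the Statistical Analysis section, so that one description of the class and one set of labels apply throughout.

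The cost is wording and one extra model term, with no new data. The downside is low power, about 25 to 29% for an interaction as large as the overall effect, so a non-significant interaction must not be read as proof of equal benefit. Because the article reports that full analysis began in December 2024, the change should be dated, with a note on whether outcome data by group had been seen.

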### Sample Size and Power Calculation

The sample size was determined to detect a clinically meaningful difference between PEAKmAAP and PEAKmAAP-DS groups combined versus the eUC group for the primary outcome measure, which is the proportion of adolescents with ACT scores of >19 at 3 months. We estimate that the proportion of participants with ACT scores of >19 at 3 months will be approximately 15% higher in the PEAKmAAP and PEAKmAAP-DS groups compared to the eUC group based on pilot work [24,40]. Using a generalized estimating equations (GEE) model for binary longitudinal data, we estimated that a sample size of 107 participants in each group will yield at least 80% power to detect the difference mentioned before. After adjusting for a 15% attrition rate, the final sample size needed will be 124 in each group (372 total). The sample size will also have at least 80% power to detect a change from a baseline of 4 between the eUC group and PEAKmAAP and PEAKmAAP-DS groups combined for the asthma self-efficacy score. The SD of the asthma self-efficacy score was determined to be 7 [21,22]. The sample size determination was performed using the GEESIZE macro in SAS Software and PASS [46-48]. All sample size calculations assumed a 2-sided significance level of 5%.

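### The named missing-data sensitivity analysis (complete-case) cannot show robustness to dropout that depends on asthma control differently by arm, and imputation hangs on an unverifiable condition with no fallback

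*Protocol article*

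**What the plan says.** The Statistical Analysis section of the Protocol article commits to intention-to-treat, under which "all randomized subjects will be included in the analysis". On missing values it says: "Missing data in primary and secondary models will be handled by multiple imputation if “missing at random” is a reasonable assumption". The next sentence is: "Results will also be reported discarding missing values as a sensitivity analysis". The article names no other missing-data sensitivity analysis and no method for the case where missing-at-random is judged unreasonable. The per-protocol models in the same section concern adherence, not unobserved outcomes.

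The primary endpoint is "the proportion of adolescents with ACT scores of >19 at 3 months", analysed with a logit link and a contrast of the two PEAKmAAP groups combined against eUC. The Sample Size and Power Calculation section expects that this proportion "will be approximately 15% higher in the PEAKmAAP and PEAKmAAP-DS groups compared to the eUC group". It reaches 124 per group "After adjusting for a 15% attrition rate", without saying at which visit that rate applies or how it splits by arm.

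**The concern.** Multiple imputation under missing-at-random and complete-case analysis both fill in, or ignore, the missing outcomes on the premise that people who look alike on the modelled variables have the same chance of control whether or not they were seen. For one binary endpoint at 3 months the two will usually agree closely. That agreement says little about whether the premise is true.

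The premise could fail here. The article itself describes adolescents as hard to engage and prone to nonadherence. The arms use different apps (asthma self-monitoring and prompts against a nutrition diary), and the primary ACT score is taken at an in-person visit. If poorly controlled adolescents leave more readily in one arm than in the other, both planned analyses can be wrong in the same direction.

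The condition attached to imputation adds a second difficulty. Whether missing-at-random is reasonable cannot be settled from the observed data, so the choice of primary method rests on a judgement with no stated consequence. If complete-case were taken as the fallback, the commitment to analyse everyone randomized would not be met.

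**Working it through.** **Inputs from the article.** 107 evaluable and 124 enrolled per group; 15% attrition; target difference about 15%, read as percentage points; two-sided 5%; two groups against one. The total is stated differently elsewhere (432 in the Abstract, 370 under Study Design); I use 124 per group.

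**Assumptions.** 15% missing at 3 months in each arm. The eUC control rate is not given; I use 30%, with a range of 15% to 40%.

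**The plan's own figure.** 107 × 1.15 = 123.05, rounded up to 124. Dividing instead, 107 / 0.85 = 125.9, gives 126; the gap of two does not matter here. With 15% missing, 124 × 0.85 = 105.4, so about 105 eUC and 210 PEAKmAAP participants are observed, out of 124 and 248.

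**1. How unseen outcomes enter.** Overall difference = 0.85 × observed difference + 0.15 × difference among the missing. With 15 points observed, the first term is 12.75. Each 10 points of arm difference among the missing moves the result by 1.5 points. The logical extremes are 12.75 − 15 = −2.25 and 12.75 + 15 = +27.75 points.

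**2. Scenarios at observed 45% versus 30%.** z = difference / √[p̄(1 − p̄)(1/n₁ + 1/n₀)], where p̄ is the pooled proportion and imputed values are treated as observed.

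| Scenario | PEAKmAAP | eUC | Difference (points) | z | p |
|---|---|---|---|---|---|
| Complete case, 210 vs 105 | 45% | 30% | 15.0 | 2.56 | 0.010 |
| Missing: 10% PEAKmAAP, 30% eUC | 0.85×0.45 + 0.15×0.10 = 39.75% | 30% | 9.75 | 1.84 | 0.066 |
| Missing: 10% in both | 39.75% | 27% | 12.75 | 2.42 | 0.015 |
| Missing: not controlled in both | 38.25% | 25.5% | 12.75 | 2.45 | 0.014 |

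With the observed-data standard error (0.0563), the second row gives z = 0.0975 / 0.0563 = 1.73, p about 0.08.

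If only 10% or 5% were missing at 3 months, the second-row scenario would give 0.90×0.45 + 0.10×0.10 − 0.30 = 11.5 points (p = 0.031) or 0.95×0.45 + 0.05×0.10 − 0.30 = 13.25 points (p = 0.013).

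**3. Tipping point.** Lower control among missing PEAKmAAP participants only, by δ. Significance is lost when 0.15 − 0.15δ = 1.96 × SE, so δ = (0.15 − 1.96 × SE) / 0.15, with SE from the observed data.

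- eUC 20%: SE 0.0510, δ about 33 points.
- eUC 30%: SE 0.0563, δ about 26 points.
- eUC 40%: SE 0.0587, δ about 23 points.
- eUC 15%: SE 0.0470, δ about 39 points, more than the 30 points available, so no shift loses it.

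**4. Which dropout biases the planned odds ratio.**

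- *Same dependence in every arm.* True control 45% vs 30%; 95% of controlled and 77% of uncontrolled participants retained. Observed: 0.4275 / 0.851 = 50.2% and 0.285 / 0.824 = 34.6%. The odds ratio is 1.909 before and after.
- *Dependence in one arm only.* True control 40% vs 30%. In PEAKmAAP, 5% of controlled and 22% of uncontrolled participants are missing (0.40×0.05 + 0.60×0.22 = 15.2%); in eUC missingness is unrelated to control. Observed PEAKmAAP: 0.380 / 0.848 = 44.8%. The difference reads 14.8 points against a true 10, and the odds ratio 1.89 against 1.56. Complete-case reports this directly. Imputation reports nearly the same unless it contains strong predictors of control.

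**The case against.** Delta grids and imputation models normally sit in a statistical analysis plan, which is not shown, and the article calls complete-case a sensitivity analysis, not the only one. That stands as a limit: a reader might infer that the trial plans no analysis beyond missing-at-random, and the article does not establish that. But the article does choose and name the analysis that is to serve as the check, and it attaches the condition to imputation. Those two choices can be judged as they stand.

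The two planned analyses are not identical in their assumptions. If imputation draws on later ACT scores and the monthly surveys, comparing it with complete-case shows whether those predictors matter. That also stands, but it still leaves untested what is assumed about outcomes beyond those predictors.

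The design limits the problem. Nutrimap is an attention control, logging is paid alike on both apps, visit payments are separate from logging payments, transport vouchers are offered, and participants are analysed whatever their adherence. Stopping the app need not mean a missing ACT score. This should lower missingness; it does not tell us who the missing are.

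Two stronger readings are tempting. One is that any loss of poorly controlled adolescents biases the result. With the planned logit link it does not, if the dependence on control is the same in every arm. The other is that 15% attrition cancels a 15-point effect because the figures match. They are different quantities, the attrition rate is not tied to the 3-month visit, and only the logical extreme reaches a reversal.

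**Conclusion.** The point holds for dropout whose link to asthma control differs between the PEAKmAAP and eUC arms. In that case neither planned analysis would reveal the problem.

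The possible size is moderate. At the assumed 15% missing and an observed 15-point effect, a one-sided departure of roughly 23 to 33 points among missing PEAKmAAP participants is needed before significance goes (eUC rates of 40% down to 20%). The 9.75-point scenario uses a 35-point departure in one arm and none in the other. Less one-sided assumptions leave the conclusion intact, and lower missingness at 3 months weakens the effect further. These figures are illustrations of sensitivity, not estimates of bias in this trial.

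The conditional wording is a separate, smaller fault that does not depend on any of these numbers. This is an improvement worth making at little cost. It is not evidence that the primary result will be wrong.

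**What to change.** - Make multiple imputation the primary method outright and remove the condition that missing-at-random be judged reasonable. This also removes the need for a fallback.
- Keep the complete-case results, described as descriptive and not as a test of the missing-data assumption.
- For ACT >19 at 3 months, add delta-adjusted multiple imputation: lower the imputed log-odds of control in the PEAKmAAP arms over a grid fixed in advance and report the value at which the conclusion changes. As a guide to range, moving from 45% to 10% control is ln(0.10/0.90) − ln(0.45/0.55) = −2.20 + 0.20 = −2.0 on the log-odds scale.
- Add one run with missing counted as not controlled in all arms.
- Report missingness at 3 months by arm, so that readers can place the tipping point.

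The cost is a few extra model runs and some wording; no new data are needed. Because the Results section says full analysis began in December 2024, the added analyses should be labelled post hoc if anyone choosing the grid has already seen outcomes by arm.
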